### Other outcomes

Additional outcomes are glucose metabolism measured as mean change from admission up to 3 months after discharge, with comparisons between groups. Diabetes status measured as the absolute number of patients with diabetes at 3 months after discharge, with comparisons between groups. Physical activity level and frailty measured at 3 months after discharge (value at a time point), with comparisons between groups.

## Measurement of outcome variables

The time points at which the different outcomes are assessed are depicted in Fig. 4. After inclusion in the study baseline testing is performed (Fig. 4, days 0 or 1). Daily during hospitalization, vital signs are noted, and blood samples are collected (Fig. 4, day 0 until discharge). At discharge, tests performed at baseline are repeated (Fig. 4). Follow-up visits take place 1 and 3 months after discharge, while a phone interview will take place 6 months after discharge (Fig. 4, follow-up).

### Standard usual care

In addition to the assessments required for the trial, patients will undergo examinations (e.g., clinical examinations, CURB-65 score, Early Warning Score (EWS), chest x-rays, 12-lead electrocardiography, and microbiological sampling (sputum, blood cultures, and urine)) prescribed by the attending physician as part of their standard usual care.

### Blood samples

Venous blood samples are collected daily in the morning (between 7 and 9 am) as part of routine tests during admission and will be analyzed the same day according to local guidelines from the Department of Clinical Biochemistry, Denmark, and thus are not affected by the study. This provides access to basic blood work such as complete blood count (white blood cell differential, red blood cell count, platelets), C-reactive protein, coagulation factors, procalcitonine, kidney function, liver function, and electrolytes. In addition to basic blood work diabetes biomarkers such as HbA1c, fasting glucose, fasting insulin, and fasting c-peptide, lipid status (total cholesterol, high-density lipoprotein (HDL) cholesterol, low-density lipoprotein (LDL) cholesterol, and triglycerides) is measured. Besides routine blood samples during admission, additional venous blood samples (plasma, serum, and whole blood) will be collected from all included patients. Plasma and serum samples will be centrifuged at 3,000 × *g* for 15 min at 4 °C and stored together with whole blood in a biobank at − 80 °C until analysis. At the day of inclusion (day 0), plasma, serum, and whole blood samples will be obtained. At days 1–5 and follow-up visits at 1 and 3 months after discharge, plasma and serum samples will be obtained. Biobank samples will be analyzed for inflammatory cytokines and chemokines (e.g., tumor necrosis factor alpha (TNF-α), interleukin (IL)-1β, IL-6, IL-8, IL-10, and IL-18).

### Study questionnaires

At the day of inclusion (day 0), information about prior medical history, socio-demography, comorbidities (Carlson Comorbidity Index (CCI) modified by Quan [27]), smoking, and drinking habits will be collected during an initial interview and supplemented with information from the patient records. Questionnaires concerning health-related quality of life (EQ-5D-5L) [28], ability to perform daily activities (Barthel Index-100) [29], physical activity level (International Physical Activity Questionnaire [IPAQ]) [30], and frailty (FRAIL scale) will be answered in cooperation with the patient at day 1. At discharge from hospital, the questionnaires EQ-5D-5L and Barthel Index-100 will be repeated. At follow-up visits 1 and 3 months after discharge and through phone interview at 6 months after discharge the questionnaires EQ-5D-5L, Barthel Index-100, IPAQ, and Frail scale will be repeated.

### Oral glucose tolerance test

A standard 2-h 75-g oral glucose tolerance test is performed following an overnight fast (8 h). Blood samples are drawn at baseline (0), 30, 60, and 120 min. The blood samples will be analyzed for p-glucose, p-insulin, and c-peptide. As a marker of stimulated insulin sensitivity, the Matsuda index will be calculated as 10,000/√[(baseline glucose × mean glucose) × (baseline insulin × mean insulin)] [31]. As a marker of fasting insulin resistance, Homeostatic Model Assessment (HOMA-IR) will be calculated as HOMA-IR = (fasting glucose × fasting insulin)/22.5 [32].

### Anthropometry and body composition

Weight is measured to the nearest 0.1 kg on an electronic scale (Seca, Hamburg, Germany). Height is measured to the nearest 0.5 cm using a stadiometer. Body mass index (BMI) is calculated as weight (kg)/height (m)^2^. Waist, hip, and arm circumferences are measured to the nearest 0.5 cm. All measurements are performed within the first 48 h of admission (day 0 or 1), at day 5, on discharge, and at follow-up visits at 1 and 3 months. Bioelectrical impedance analysis (BIA) (BioScan touch i8, Maltron International Ltd, UK) is performed at day 0 or 1, at day 5, on discharge, and follow-up visits at 1 and 3 months to assess changes in the total fat-free mass, fat mass, and body fluids/hydration. Dual-energy x-ray absorptiometry (DXA) scans (Prodigy, GE Healthcare, Nederland) are used to assess the regional distribution of lean body mass and fat mass at days 0 or 1, day 5, and follow-up visits at 1 and 3 months.

### Physical activity

IPAQ will be used to obtain information on the level of physical activity prior to hospital admission, ambulatory visits, and phone interview. Posture allocation and physical activity behaviors are measured using 3-axial accelerometer-based physical activity monitors (Axivity AX3, Newcastle, UK). All patients are equipped with accelerometers placed on the right thigh (posture allocation) and on the right side of the lower back (activity intensity) at admission and until discharge (a maximum of 7 days). At discharge and at follow-up visits at 1 and 3 months after discharge, the accelerometers will be re-attached and collect activity data for further 7 days.

### Muscle strength and functional ability

Muscle strength is measured using the handgrip test (SAEHAN DHD-1 Digital Hand Dynamometer, SAEHAN Corporation, South Korea) as an indicator of overall muscle strength, while the 30-s chair stand test (CST) is used to evaluate the functional ability by measuring lower body strength. Both tests are performed at days 0 or 1, day 5, on discharge, and follow-up visits at 1 and 3 months after discharge.

### Strategies for preventing loss to follow-up

As the study has a relatively long follow-up period, different strategies have been incorporated into the study to minimize loss to follow-up. In order to increase patient’s commitment to the study, the research personal is trying to establish a bond with the patient by having the same personal performing tests, instructing exercise sessions, and scheduling follow-up visits. As the patient is being discharged contact information (phone number and email address) is collected. The follow-up visits should be as flexible and convenient for the patient as possible; therefore, the follow-up visits are offered either as hospital or home visits. To minimize absences from planned follow-up visits, patients are reminded about their upcoming visit in the study. After completion of the first follow-up visit, the next visit is scheduled in advanced to reduce the risk of not being able to get hold of the patient.

### Safety

The safety of initiating exercise in patients early during hospitalization is an area of interest. In a newly published systematic review of patients hospitalized with acute respiratory conditions, a total of 17 adverse events were reported across 1146 participants who completed a total of ~ 7420 exercise sessions [33]. Only 1 serious adverse event occurred and resolved spontaneously in the group performing low-intensity exercise [34]. Therefore, there is no clear relationship between the prescription of exercise intensity and adverse events [33]. However, to ensure that our exercise interventions are delivered safely, oxygen saturation and heart rate are continuously monitored during exercise by pulse oximetry (PalmSAT 2500 Series Pulse Oximeter, NONIN Medical Inc., Minneapolis, USA). Any serious adverse events will be reported to the scientific ethics committee of the Capital Region of Denmark which will decide whether any additional precautions should be taken.

## Statistical power and sample size calculations

The sample size calculation is performed using www.powerandsamplesize.com and is based on the primary outcome, length of hospital stay. The expected reduction in length of hospital stay is based on data from a previous study showing a reduction (3.9 days vs. 6.0 days) for patients hospitalized with CAP randomized to either early mobilization or standard usual care [18]. The number of patients with CAP is based on a 2-day difference in length of hospital stay between CAP patients receiving standard usual care compared to standard usual care combined with daily physical training. The standard deviation for this calculation is 3.5 days, as previous observed [18]. Assuming an estimated drop-out rate of 15%, inclusion of 210 patients (70 patients in each group) will provide a power of > 0.8 at a two-sided significance level of 0.025, adjusted for multiple comparisons (0.05/2).

## Challenges and protocol changes due to the coronavirus disease (COVID)-19

Due to the COVID-19 pandemic and a national wide lockdown starting in March 2020, the study was suspended from March 13, 2020, to April 21, 2020. The recruitment process was again suspended from December 7, 2020, to January 4, 2021, due to the second national wide lockdown. After the second lockdown, the steering committee decided to expand the study inclusion to patients with COVID-19 CAP. As COVID-19 patients is isolated during hospitalization, the exercise sessions are limited to the patient rooms, meaning that especially the exercise booklet group is restricted to primarily strengthening exercises. The COVID-19 pandemic has resulted in missed follow-up visits both hospital and home visits as patients have been unwilling to engagement in research-related activities due to the risk of being exposed to COVID-19. Moreover, follow-up visits are performed more often as home visits.

## Statistical analysis and reporting

The results will be reported in accordance with the Consolidated Standards of Reporting Trials (CONSORT) [35]. Sensitivity analysis for missing data will be performed.

### Pre-planned analysis

Available-case analyses will be carried as the main aim is to evaluate the efficacy of the interventions. This means that patients will contribute to the statistical analyses until they drop-out or the study is terminated. Also, as patient drop-out in most cases will be caused by factors, which will happen independently of this study, missing at random will most likely be an acceptable assumption. Additionally, subgroup analyses for patients without COVID-19 CAP will be carried out as patients with COVID-19 CAP may stay longer at the hospital.

For the primary outcome (length of hospital stay), analysis of covariance will be performed to quantify differences between groups. The following covariates will be included in the model: age, gender, CURB-65 score, BMI, and total number of comorbidities (categories 0, 1, 2, > 2). The estimated mean difference (in changes) between the standard usual care group and the two exercise groups (standard usual care vs. exercise booklet and standard usual care vs. in-bed cycling) with the corresponding adjusted confidence interval (CI) and *p* values will be reported. Both CIs and *p* values will be adjusted utilizing correlations between estimates and tests in a less conservative way compared to Bonferroni adjustment [36].

Survival analysis with Kaplan-Meier estimation and Cox proportional hazards regression will be performed to explore differences between groups in time to readmission. Hazard ratios comparing the standard usual care group with the two exercise groups (standard usual care vs. exercise booklet and standard usual care vs. in-bed cycling) will be estimated and reported together with corresponding CIs and *p* values. Kaplan-Meier estimation and Cox proportional hazards regression will be performed to explore differences between groups in time to mortality. Hazard ratios comparing the standard usual care group with the two exercise groups (standard usual care vs. exercise booklet and standard usual care vs. in-bed cycling) will be estimated and reported together with corresponding CIs and *p* values. For readmission, data will be censored 3 months after discharge, while for mortality, censoring will occur 6 months after discharge.

For secondary outcomes (total lean mass, total fat mass, total fat-free mass, leg lean mass, trunk fat mass, EQ-5D-5L score, Barthel Index-100 score, grip strength, 30-s CST, systemic inflammation, and physical activity [AX3]), linear mixed models with treatment by time interaction as a fixed-effects term and patient-specific random intercepts will be fitted to explore differences in changes from baseline between groups. Specifically, the estimated mean difference (in changes) between the standard usual care group and the two exercise groups (standard usual care vs. exercise booklet and standard usual care vs. in-bed cycling) with corresponding CIs and *p* values will be reported. Logarithm transformations will be applied where appropriate (to handle right-skewed distributions), and resulting estimates and CIs will be back-transformed accordingly.

Likewise, for exploratory outcomes (glucose metabolism), linear mixed models with treatment by time interaction as a fixed-effects term and patient-specific random intercepts will be fitted to explore differences in changes from baseline between groups. Specifically, the estimated mean difference (in changes) between the standard usual care group and the two exercise groups (standard usual care vs. exercise booklet and standard usual care vs. in-bed cycling) with corresponding CIs and *p* values will be reported.

For other categorical outcomes (IPAQ score, diabetes status, and frailty score), differences between groups at 3 months will be explored by the chi-squared test (r × c tables) and expressed as counts and percentages, and *p* values will be reported. In all statistical analyses, *p* values < 0.05 will be considered significant.

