**Methods:**

This study is a randomized controlled trial with three parallel experimental arms. Based on a sample size calculation, a total of 210 patients admitted with CAP at Nordsjællands Hospital, Hillerød, Denmark, will be recruited. Patients will be randomly allocated (1:1:1) to either (1) standard usual care, (2) standard usual care combined with in-bed cycling, or (3) standard usual care combined with exercises from a booklet. The primary outcome is differences in length of hospital stay between groups, with secondary outcomes being differences between groups in time to (1) 90-day readmission and (2) 180-day mortality. Further secondary outcomes are differences in changes from baseline between groups in (3) lean mass, (4) fat mass, (5) fat-free mass, (6) physical capacity, (7) health-related quality of life, (8) systemic inflammation, and (9) physical activity level after discharge. Data on length of hospital stay, readmission, and mortality will be collected from patient files, while total lean, fat, and fat-free mass will be quantitated by dual-energy x-ray absorptiometry and bioelectrical impedance analysis. Physical function will be assessed using grip strength, 30-s chair stand tests, and Barthel Index-100. Health-related quality of life will be assessed with the EQ-5D-5L questionnaire. Systemic inflammation will be assessed in blood samples, while accelerometers are used for measuring physical activity.

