### Primary outcome

The primary outcome is length of hospital stay from the time of admission until discharge, with comparison of the groups.

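### One available-case rule covers all outcomes, so patients who drop out before discharge leave the primary analysis although the hospital record holds their length of stay

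*Protocol article*

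**What the plan says.** The section Pre-planned analysis sets the rule and its reason: "Available-case analyses will be carried as the main aim is to evaluate the efficacy of the interventions". It then explains what this means: "patients will contribute to the statistical analyses until they drop-out or the study is terminated". The rule stands ahead of all the outcome-specific paragraphs and excepts none of them. The same section argues that most drop-out will have causes unrelated to the study, so that "missing at random will most likely be an acceptable assumption". Statistical analysis and reporting adds only this: "Sensitivity analysis for missing data will be performed".

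The primary outcome is a single value per patient: "The primary outcome is length of hospital stay from the time of admission until discharge". Table 2 computes it as discharge date minus admission date. It is analysed by ANCOVA with age, gender, CURB-65, BMI and number of comorbidities as covariates.

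The abstract gives the data source: "Data on length of hospital stay, readmission, and mortality will be collected from patient files". The Follow-up section confirms electronic capture of readmission and mortality up to 6 months after discharge.

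The sample size section, which is based on length of stay, states: "Assuming an estimated drop-out rate of 15%, inclusion of 210 patients (70 patients in each group) will provide a power of > 0.8".

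**The concern.** Length of stay does not exist until discharge. If a patient contributes only up to drop-out, one who leaves the study on day 2 has no value and falls out of the primary analysis, yet the discharge date will still be in the file. For readmission and mortality the same sentence, taken literally, ends follow-up at drop-out even though the record continues.

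Two things are at stake. The first is power given up for no return. The second is the randomised comparison itself: once patients are removed after allocation, the arms are comparable only if removal is unrelated to outcome given the covariates, or acts alike in all arms. Causes unrelated to the study do not secure this. Clinical worsening may have nothing to do with the study and still lengthen the stay. Because it happens after randomisation, baseline covariates capture it only in part. An efficacy aim is not a reason to leave out randomised patients of a superiority trial whose outcome is on file.

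**Working it through.** **Inputs from the protocol.** Difference Δ = 2 days, SD σ = 3.5 days, two-sided α = 0.025 per comparison (0.05/2), power 0.8, drop-out 15%, 70 per arm.

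**1. The plan's own figure.** n = 2σ²(z₀.₉₈₇₅ + z₀.₈)²/Δ² = 2 × 12.25 × (2.241 + 0.842)²/4 ≈ 58.2, so 59 per arm. Then 59/0.85 = 69.4, so 70 per arm and 210 in total. The stated size is reproduced. It corresponds to counting 15% of patients as lost to the primary outcome.

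**2. Power with and without the loss.** Power = Φ(Δ/(σ√(2/n)) − 2.241).
- n = 59.5 (70 × 0.85): Φ(3.117 − 2.241) = 0.809.
- n = 70: Φ(3.381 − 2.241) = 0.873.

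A t-based check gives 0.796 at 59, 0.804 at 60 and 0.866 at 70 per arm. The difference detectable with 80% power is 1.98 days at 59.5 and 1.82 days at 70 per arm. The gap of about 6 points is the most that can be lost, because it requires all 15% to leave before discharge. Patients lost at the 1- or 3-month visit already have a length of stay.

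**3. Possible bias (assumed inputs).** The documents give no drop-out rate by arm, no in-hospital rate, and no length of stay for drop-outs. Take no true effect and a mean stay of 6 days in every arm (the usual-care figure cited in the sample size section). If a share p drops out with mean stay m, the completers' mean is (6 − p·m)/(1 − p). With 15% in a training arm and 5% in control:
- m = 8: 4.8/0.85 − 5.6/0.95 = 5.65 − 5.89 = −0.25 day.
- m = 10: 4.5/0.85 − 5.5/0.95 = 5.29 − 5.79 = −0.50 day.

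With equal p and equal m in all arms the difference is 0. If the two rates are exchanged, the sign reverses.

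A second illustration keeps overall drop-out at 15%: 20% in each training arm and 5% in control. Let D be the drop-outs' mean stay minus the completers'. The shift is (0.20 − 0.05) × D, which is 0.30 day for D = 2 and 0.53 day for D = 3.5. With 56 and 66.5 patients left, SE = 3.5√(1/56 + 1/66.5) = 0.635. The chance of a false finding for training, nominally 1.25%, becomes 3.8% or 7.9%.

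All these figures are unadjusted. The planned ANCOVA would remove whatever part is explained by its covariates.

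**The case against.** The strongest reply is that the sentence is general and the word available may already cover a discharge date on file. The protocol nowhere calls the analysis per-protocol and nowhere says that drop-out means stopping training. A reader might infer that patients who give up the daily sessions are excluded, and hence that the exercise arms must lose more. The documents do not support this: a patient who stops exercising but stays in the trial keeps a length of stay, and controls also undergo tests and can leave.

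The 15% is a routine allowance. It does not prove whom the primary analysis will exclude, and the losses the article describes are mostly missed follow-up visits. A reader might also infer that the randomised comparison is lost for all three record-based outcomes. That goes too far. Patients who leave after discharge keep their length of stay and contribute time to readmission and mortality, for which the survival paragraph names only fixed censoring at 3 and 6 months. Complete-case ANCOVA is unbiased if drop-out depends only on arm and the listed covariates. A sensitivity analysis is promised, and the Fig. 2 legend promises reasons for exclusion.

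These points limit the size and certainty of the harm. They do not change the rule as written, which ends contribution at drop-out and excepts nothing. A sensitivity analysis of unstated content does not replace using recorded values in the primary analysis, and baseline adjustment does not reach worsening after randomisation.

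**Conclusion.** The point holds as a defect in the stated analysis rule: followed literally, it discards primary-outcome data that the hospital record holds. The certain part is qualitative. The cost in power is at most about 6 points (0.87 to 0.81), reached only if all 15% leave in hospital, and the plan still meets its target under its own method, so this is not a failed sample size. Bias requires drop-out that differs by arm and is related to length of stay beyond age, gender, CURB-65, BMI and comorbidities. Under the assumed patterns it is some 0.25 to 0.5 day against a 2-day target. It is tempting to conclude that the rule favours training. The documents give no rates by arm from which to conclude that, and the shift may be zero or run the other way.

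**What to change.** In Pre-planned analysis, state that length of stay, readmission and mortality are analysed from the hospital record in all randomised patients by allocated arm, whether or not they continued training or tests, and that only patients who withdraw consent to use of their records are excluded. State also that follow-up for readmission and mortality runs to the fixed 3- and 6-month limits regardless of drop-out. Keep available-case analysis for outcomes that need a visit or test, and as a supportive analysis of the three record-based outcomes.

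The cost is wording, since the data are already captured. The downside is that the estimate includes patients who trained little and may be slightly diluted. If the sponsor always meant to use record data after drop-out, the current sentence says otherwise and still needs the correction.

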**Fig. 1 Fig1:**
[figure not shown]
Breaking the vicious cycle of hospitalization, disability, and poor prognosis through physical training. Dark colors, e.g., dark gray, dark blue, and dark green, indicate processes which takes place in hospital during hospitalization. Lighter colors, e.g., light gray, light blue, and light green, indicate time periods, which takes place at home after discharge

Previous studies have shown that only 10–14 days of bed rest leads to a substantial loss of lower extremity muscle mass and muscle strength, increase in visceral fat, and impairments in insulin sensitivity in healthy individuals [13–16]. Moreover, these bed rest-related changes were associated with a reduction in physical activity level during the week following bed rest [13]. However, early mobilization of patients with CAP within the first 24 h of hospitalization has been shown to decrease length of hospital stay by 1.1 to 2.1 days without increasing the risk of adverse events [17–19]. In addition, for every increase in the daily step count above 500 steps, length of hospital stay was reduced by 11% among patients with CAP [6]. Moreover, we have previously shown that initiating supervised early pulmonary rehabilitation of patients with acute exacerbation of chronic obstructive pulmonary disease (COPD) during hospitalization is superior to standard usual care in terms of improving prognosis (reduces the risk of COPD-related hospital readmissions), health-related quality of life, and walking distance [20].

Even though international guidelines for the management of patients hospitalized with CAP recommend early mobilization as part of standard of care for CAP [21], the physical activity level among patients hospitalized with CAP remains low. Despite the emerging evidence that physical activity during hospitalization for respiratory conditions is beneficial in terms of improving functional outcomes, it is not consistently prioritized in clinical practice. Therefore, interventions that increases physical activity and interrupt sedentary time during hospitalization are crucial (Fig. 1).

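### The primary three-arm ANCOVA pools one residual variance by default, so the two adjusted confidence intervals would be modestly too narrow if both training arms shorten stay and narrow its spread

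*Protocol article*

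**What the plan says.** Under Pre-planned analysis the article states: "For the primary outcome (length of hospital stay), analysis of covariance will be performed to quantify differences between groups". The model is adjusted: "The following covariates will be included in the model: age, gender, CURB-65 score, BMI, and total number of comorbidities", the last in four categories. Two differences are reported, usual care against booklet and usual care against in-bed cycling. Their intervals and p values are "adjusted utilizing correlations between estimates and tests in a less conservative way compared to Bonferroni adjustment". No variance estimator is named. The log transformation for right-skewed data appears only in the paragraph on secondary outcomes, so the primary outcome is analysed in days.

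The sample size section plans on an absolute effect: "The number of patients with CAP is based on a 2-day difference in length of hospital stay". It uses one SD, 3.5 days, for all arms, and cites an earlier trial with mean stays of 3.9 and 6.0 days. The Background gives activity effects in two forms: reductions of 1.1 to 2.1 days with early mobilization, and a relative one, "for every increase in the daily step count above 500 steps, length of hospital stay was reduced by 11% among patients with CAP".

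**The concern.** An ANCOVA named without qualification estimates one residual variance from all arms. With 1:1:1 allocation, that also implies a correlation of about 0.5 between the two contrasts. Both features are right if the arms have the same spread.

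That assumption is least secure when the intervention works. Stay is bounded at zero, and an effect that acts proportionally would shrink the SD along with the mean. Usual care would then have the largest variance and would enter both contrasts, while two of the three arms feeding the pooled variance would be the narrower ones. Equal allocation does not protect against this. The reported precision of the primary result would be overstated when both modalities succeed. If only one modality succeeds, the comparison of the effective arm would lose some power and the inert arm would look somewhat more favourable than it should.

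**Working it through.** **1. The plan's own figure.** Inputs from the sample size section: difference 2 days, SD 3.5 days, two-sided alpha 0.025, power above 0.8, dropout 15%. The two-sample formula gives 59 per arm (power 0.806). 59/0.85 = 69.4, rounded up to 70 per arm, 210 in total. The stated figure reproduces.

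**2. Pooled against true standard error, both modalities effective.** Let s0 be the usual-care SD, s1 = k·s0 the SD in each training arm, and n = 59. The article does not give k; it is an assumption, shown over a range.

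- Pooled SE² = (2/n)·(s0² + 2·s1²)/3
- True SE² = (s0² + s1²)/n
- True minus pooled = (s0² − s1²)/(3n), positive whenever k < 1

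For k = 4/6: s1 = 2.333; pooled SE = √[(2/59)·(12.25 + 2·5.444)/3] = 0.511; true SE = √[(12.25 + 5.444)/59] = 0.548; ratio 0.93.

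With s0 = 3.5 and a large-sample Dunnett-type critical value of 2.212:

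| k | pooled/true SE | coverage of one CI (nominal 97.3%) | joint coverage (nominal 95%) |
|---|---|---|---|
| 1.0 | 1.000 | 97.3% | 95.0% |
| 0.9 | 0.982 | 97.0% | 94.6% |
| 0.8 | 0.963 | 96.7% | 94.1% |
| 0.65 (= 3.9/6.0) | 0.930 | 96.0% | 93.3% |
| 0.5 | 0.894 | 95.2% | 92.5% |

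At k = 0.65 the interval half-width is 1.12 days where 1.20 is needed. The true correlation between the contrasts is s0²/(s0² + s1²) = 12.25/(12.25 + 5.176) = 0.70, not 0.5.

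**3. Only one modality effective, k = 0.65.** The pooled variance is (2·12.25 + 5.176)/3 = 9.892, so the pooled SE is √(2·9.892/59) = 0.579.

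- Effective arm: true SE 0.543, ratio 1.07, so its interval is about 7% too wide.
- Inert arm: true SE √(2·12.25/59) = 0.644, ratio 0.90, so its interval is about 10% too narrow. Its rejection rate is 2·[1 − Φ(2.212·0.899)] ≈ 4.7%, against a nominal 2.7%.

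**4. With covariates.** The formulas above ignore covariates, so the ANCOVA was simulated with seven covariate columns (age, gender, CURB-65, BMI, three comorbidity indicators). Assumptions: R² 0.2, 59 per arm, means 6 and 4 days, usual-care SD 3.5, gamma or normal data, 20,000 trials per scenario.

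- Both effective, pooled variance: joint miss rate about 5% with equal SDs, 5.8% with SD following the square root of the mean, 6.5–6.7% with SD proportional to the mean (model SE 0.467, true SE about 0.50 days).
- Both effective, arm-specific or HC2 variances: about 4.6–5.2%.
- One effective, proportional SD: the inert arm is rejected in about 4.2–4.7% of trials, against about 3% with arm-specific variances. Power for the effective arm is about 0.945–0.955, against 0.957–0.969.
- Normal and gamma data give nearly the same results, so this is separate from skewness.

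**The case against.** The strongest reply has four parts.

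- **The article does not fix a variance estimator.** It neither states a common variance nor excludes robust errors, and an analysis plan that is not shown may settle this. That stands. A reader might infer that the plan commits to equal variances, but the text supports only the usual default of the named method. The point survives as a preference for a better default, not as a charge of omission.
- **Unequal spread is hypothetical.** This stands too. The only SD given is 3.5 days. The 11% figure is an association with step count and says nothing about variance by randomised arm. The Background also gives effects in absolute days, and the sample size uses an absolute difference with one SD. With equal SDs there is no defect.
- **Error control holds.** A reader might infer that the type I error is inflated. It is not: under the global null the arms share one distribution. If only one arm works, the inert arm is the sole true null, and its rejection rate of 4.2–4.7% stays within the 5% family-wise level. The lower rate of about 3% is slack in a single-step adjustment.
- **The size is modest and the direction is not uniform.** At k = 0.65 each single interval still covers 96.0%, and the half-width differs by 0.08 days. A reader might infer that both intervals are always too narrow, but that requires both modalities to narrow the spread. If only one does, the effective arm's interval is too wide.

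What remains is that the default interval can miss its stated joint coverage when both modalities work, and an almost costless alternative does not.

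**Conclusion.** The point holds as a modest matter of accuracy in the primary intervals. Under a pooled three-arm ANCOVA with both modalities effective, the standard errors are about 2% too small at an SD ratio of 0.9 and about 7% too small at 0.65. The joint miss rate rises from about 5% to 5.8% or 6.5–6.7%, depending on how strongly the SD follows the mean. These figures rest on 59 analysed per arm, means of 6 and 4 days, a usual-care SD of 3.5, covariates explaining 20% of variance, and an SD ratio that the article does not supply. The 210 patients stand, and nothing stated in the article is contradicted. The case for acting is that the inaccuracy arises where training works, and the Discussion hopes to learn which exercise modalities can be implemented.

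**What to change.** Keep the ANCOVA, the covariates, the two contrasts and the correlation-based adjustment. Add one sentence: the covariance matrix of the two contrasts is computed from arm-specific residual variances (or the HC2 estimator) and passed to that adjustment, so that the standard errors and the correlation both reflect the observed spread in each arm.

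The cost is one line of analysis code. If SDs are in fact equal, the power loss is at most about 0.3–0.4 points (for example 0.869 to 0.866 in the covariate simulation). HC3 is a less suitable choice here: it is slightly conservative in this model (miss rate about 3.8–4.6%) and loses about 1.2–1.5 points of power if SDs are equal.
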